### Nature of nutrition care

Nutrition care will follow the Nutrition Care Process developed by the Academy of Nutrition and Dietetics, Chicago USA. This involves assessment, diagnosis of nutrition problem, intervention, monitoring and evaluation [52]. Australian and New Zealand evidence-based guidelines for the nutritional management of kidney transplant recipients will be used [53, 54].

### Standard care group

Participants randomised to the standard care group will receive standard post-transplant care as per usual local practice. This includes immunosuppressive medications to prevent rejection and other treatments under the direction of the treating physician and renal transplant team. Standard immunosuppression includes a calcineurin inhibitor (cyclosporine or tacrolimus as determined by the treating physician), mycophenolate, steroids, and basiliximab as induction therapy.

Current standard nutrition care after kidney transplantation at Auckland City Hospital includes assessment by a renal dietitian during the inpatient stay. Patients are given resources guiding them on healthy eating and food safety after transplant, and nutrition interventions to address any identified nutritional problems. Standard outpatient nutrition care involves an individual consultation with a specialist renal dietitian at 1, 3 and 12 months post-transplant alongside regular physician appointments.

### Intensive nutrition intervention group

Patients randomised to the intensive nutrition intervention group will, in addition to standard care, receive more frequent counselling with a specialist renal dietitian throughout the trial. These will commence at one month post-transplant and include an additional 8 visits overall compared to the standard care group (see Table 1). Participants will also receive individualised assessment and advice regarding physical activity and exercise, via formal consultations with an exercise physiologist at 2 months, 3 months and 6 months post-transplant.

**Table 1 Tab1:** **Schedule of nutrition assessment**, **education and advice provided by renal dietitian and exercise physiologist** (**intensive nutrition intervention group**)

**Months 1** **-** **3**	**Fortnightly** review with dietitian to undertake initial assessments, determine progress, goals and adherence to recommendations
	Full review of dietary intake and adequacy of adherence to recommendations to be undertaken at 1 month and 3 months (including 3-day food diary and analysis)
	Exercise advice (including a consultation with an exercise physiologist at 8 and 12 weeks to provide tailored advice) regarding physical activity and a review of physical activity adherence
**Months 4** **-** **6**	**Monthly** review with dietitian to assess progress, goals and adherence to recommendations, and give further education and advice as appropriate
	Full review of dietary intake and adequacy of adherence to recommendations to be undertaken at 6 months (including 3-day food diary and analysis)
	Exercise advice (including a consultation with an exercise physiologist at 6 months to provide tailored advice) regarding physical activity and a review of physical activity adherence
**Months 7** **-** **12**	**Bi** **-** **monthly** review with dietitian to assess progress, goals and adherence to recommendations, and give further education and advice as appropriate
	A final review of diet history and adequacy of adherence to recommendations to be undertaken at 12 months (including 3-day food diary and analysis)
	Exercise advice to promote adequate physical activity and review of physical activity adherence

Individualised nutrition counselling will be provided using motivational interviewing techniques to encourage quality engagement. Personal nutrition plans will be developed using S.M.A.R.T. action steps, i.e. specific, measureable, achievable, relevant and time-limited [55].

Prior to full reviews at 1, 3, 6 and 12 months, a self-administered 3-day food diary record will be completed by participants and analysed using appropriate analysis software (e.g. FoodWorks® Professional [Xyris software]). Dietary intake data will be compared to evidence-based recommendations on nutrient requirements after renal transplant and used to guide nutrition prescriptions. At follow-up reviews, renal dietitians will assess progress, goal setting and adherence to dietary recommendations. Adherence will be measured using rulers to assess motivation to change, level of achievement of patient-centred goals and review of action steps taken in patient action plans.

### Primary and secondary outcomes

The primary outcome will be body weight at 6 months post-transplant, adjusted for weight at baseline (one month post-transplant), pre-existing obesity (BMI ≥30 kg/m^2^), and gender.

Secondary outcomes will include the following: change in weight and other anthropometric measures at 3, 6 and 12 months post-transplant; change in gold-standard body composition parameters post-transplant; validity of bio-electrical impedance assessment as compared with gold-standard body composition analysis in kidney transplant recipients; change in biochemical measures post-transplant (e.g. lipid profile and markers of insulin resistance); adherence to dietary advice in the intervention group; level of physical activity and physical functional capacity in transplant recipients; and quality of life in transplant recipients. In addition, a cost-effectiveness analysis of intensive nutrition intervention will be undertaken taking into account the costs of additional dietitian input (including missed visits), changes in weight and quality of life.

In order to determine the feasibility of undertaking larger multi-centre trials of nutrition interventions to reduce the incidence or severity of diabetes after transplantation, the difference in HbA1c observed between the intervention and standard care groups at 12 months will be reported as an exploratory feasibility outcome.

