**Methods/Design:**

The effect of **INTE**nsive **N**utrition interventions on weight gain after kidney **T**ransplantation (INTENT) trial is a single-blind (outcomes assessor), randomised controlled trial to assess the effect of intensive nutrition interventions, including exercise advice, on weight gain and metabolic parameters in the first year after transplantation. Participants will be randomised during the first post-transplant month to either standard care (four visits with a renal dietitian over twelve months) or intensive nutrition intervention (eight visits with a renal dietitian over the first six months, four visits over the second six months, and three visits over the first six months with an exercise physiologist). In the intensive intervention group, nutrition counselling will be provided using motivational interviewing techniques to encourage quality engagement. Collaborative goal setting will be used to develop personalised nutrition care plans. Individualised advice regarding physical activity will be provided by an exercise physiologist. The primary outcome of the study is weight at six months after transplant, adjusted for baseline (one month post-transplant) weight, obesity and gender. Secondary outcomes will include changes in weight and other anthropometric measures over 12 months, body composition (in vivo neutron activation analysis, total body potassium, dual-energy X-ray absorptiometry, and bioelectrical impedance), biochemistry (fasting glucose, lipids, haemoglobin A1c and insulin), dietary intake and nutritional status, quality of life, and physical function.

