In kidney transplant patients, the few studies that have considered the effects of nutrition and exercise interventions on bodyweight within the 12 months after transplant have had inconsistent results: significantly less weight gain [49], a significant reduction in weight gain from baseline for males [50], or no effect on bodyweight [51]. However, the interpretation of results is limited by the study designs; two studies were non-randomised [49, 50] and one was designed to assess the effects of the intervention on hyperlipidaemia [51].

Overall, there is a need to develop effective interventions to minimise the detrimental effects of weight gain and obesity on long-term kidney transplant outcomes. Randomised controlled trials are needed to assess whether nutrition interventions are likely to be effective in preventing weight gain after kidney transplantation.

The effect of **INTE**nsive **N**utrition interventions on weight gain after kidney **T**ransplantation (INTENT) trial is a randomised controlled trial designed to evaluate the effect of an intensive nutrition intervention, including tailored advice regarding exercise and physical activity, on weight gain in the first year following kidney transplantation. In addition, detailed measures of the effects of the nutrition intervention on other anthropometric measures, body composition, glucose metabolism and biochemical markers of metabolic risk, functional capacity and quality of life will be performed. The trial will also provide data on the feasibility of conducting larger trials of nutrition interventions to reduce the incidence or severity of diabetes after kidney transplantation.

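### The cost-effectiveness analysis names dietitian input as its one cost, although the package it evaluates also contains three exercise-physiologist consultations given only to the intensive arm

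*Protocol article*

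**What the plan says.** Under Primary and secondary outcomes, the Protocol article states that "a cost-effectiveness analysis of intensive nutrition intervention will be undertaken", and gives its inputs as "taking into account the costs of additional dietitian input (including missed visits), changes in weight and quality of life". That is one cost item and two effects.

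The intervention is defined more widely. The Background describes it as "an intensive nutrition intervention, including tailored advice regarding exercise and physical activity". The section on the intensive nutrition intervention group says that its dietitian visits "include an additional 8 visits overall compared to the standard care group", and adds "formal consultations with an exercise physiologist at 2 months, 3 months and 6 months post-transplant". The abstract gives the intensive arm twelve dietitian visits (eight in the first half-year, four in the second) and three exercise-physiologist visits, and Table 1 carries both professions in its title.

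For controls, the abstract lists "standard care (four visits with a renal dietitian over twelve months"). The Standard care group section describes an inpatient dietitian assessment and outpatient dietitian consultations at three time points. Neither place mentions an exercise physiologist. Nowhere does the article say that the physiologist consultations will be costed.

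**The concern.** A cost-effectiveness ratio needs its cost and its effect to refer to the same thing. Here the effect is the between-arm difference in weight and quality of life. It belongs to the whole randomised package, because the design cannot separate what the dietitian achieved from what the exercise physiologist achieved. The cost, as worded, belongs to the dietitian part alone.

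The omission works in one direction. The physiologist visits occur in the intensive arm and not in the control arm, so leaving them out can only lower the incremental contact cost. If the intervention shows a benefit, the contact cost per kilogram of weight gain avoided, or per unit of quality of life gained, would look better than the package delivers. Anyone using the figure to plan a larger trial or a service would be pricing one of its two staff inputs.

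**Working it through.** **Inputs from the Protocol article**
- Intensive arm, abstract: 8 dietitian visits in the first six months, 4 in the second six months, and 3 exercise-physiologist visits.
- Standard arm, abstract: 4 dietitian visits, no exercise physiologist.
- Intensive nutrition intervention group section: 8 additional dietitian visits; physiologist consultations at months 2, 3 and 6.

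**Input that the article does not give**
- c, the cost of one physiologist visit divided by the cost of one dietitian visit. Assumed range 0.5 to 1.5, with 2 as a further check. Visit length and pay rate are both folded into c.

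**Step 1. Reproduce the stated figure.** Additional dietitian visits = (8 + 4) − 4 = 8, as stated.

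A cross-check uses Table 1. Fortnightly review read as weeks 4, 6, 8, 10 and 12 gives 5 visits, monthly review in months 4 to 6 gives 3, and bi-monthly review in months 7 to 12 gives 3, so 5 + 3 + 3 = 11. Against the 3 outpatient consultations of standard care, 11 − 3 = 8 again. The abstract's four visits in the second six months and Table 1's bi-monthly schedule do not match, but the difference of 8 comes out both ways.

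**Step 2. Count all incremental contacts.** 8 dietitian + 3 physiologist = 11. Share not covered by the named cost = 3/11 = 27%.

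**Step 3. Convert to cost, per participant and in units of one dietitian visit.** All scheduled visits are counted, in keeping with the plan's inclusion of missed visits.
- Cost as written: 8
- Cost of the full package: 8 + 3c
- Share of incremental contact cost omitted: 3c/(8 + 3c)
- Full cost relative to the cost as written: 3c/8 higher

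| c (assumed) | Omitted share | Full cost above cost as written |
|---|---|---|
| 0.5 | 1.5/9.5 = 16% | 1.5/8 = 19% |
| 1.0 | 3/11 = 27% | 3/8 = 38% |
| 1.5 | 4.5/12.5 = 36% | 4.5/8 = 56% |
| 2.0 | 6/14 = 43% | 6/8 = 75% |

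**Step 4. Effect on the ratio.** For a given positive effect, the ratio built on contact cost falls by the omitted share. If the effect is nil or adverse, the ratio has no useful reading and only the understated incremental cost remains.

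**The case against.** The strongest reply is that the sentence lists something to be taken into account and does not say that nothing else will be. It calls the object of the analysis the intensive intervention, which the article defines as including exercise advice, so costing the whole package is compatible with the text. The article is also condensed: perspective, unit costs and time horizon are absent, as one would expect, and a fuller economic plan could add the physiologist.

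Part of this stands. A reader might infer that the plan excludes physiologist costs by decision. The text does not support that, since it contains no word of limitation. A reader might also take 16% to 36% as the size of the bias. The article has no unit cost from which any such figure could be derived, and the 27% is a share of contacts, not of money.

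The point survives nonetheless. It does not turn on missing detail. The sentence states the cost input, and does so finely enough to mention missed dietitian visits, yet the second profession is absent there and is costed nowhere else. Reading dietitian input as shorthand for both professions is strained, because the article keeps them apart in the abstract, in the intervention section and in the title of Table 1. An analyst who followed the sentence as written would cost dietitian time alone.

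**Conclusion.** The point holds in a limited form. As worded, the cost side covers one of the package's two staff inputs while the effect side credits both. If the analysis is costed that way, 3 of 11 incremental contacts (27%) are left out and the incremental contact cost is understated in the intervention's favour. The count and the direction rest on the article's own visit schedule. The amount in money rests wholly on the assumed ratio c: about 16% to 36% for c from 0.5 to 1.5, as illustration only.

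Two wider conclusions are tempting and are not supported. One is that the trial's cost per kilogram is biased low. That would require both that the visits are in fact left uncosted and that the intervention shows a benefit. The other is that the analysis must also add food-diary analysis and hospital admissions. Diary analysis feeds the dietitian's full reviews and can already fall under dietitian input. Costing admissions is a choice of perspective, and in a trial of up to 32 participants a few admissions could dominate the result. Neither corrects a stated error.

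This is an additional analysis, and the primary outcome, its ANCOVA and the sample size are untouched. It should still be corrected, because the correction is small.

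**What to change.** Reword the cost item in Primary and secondary outcomes to: the costs of all additional intervention contacts, i.e. dietitian visits and exercise-physiologist consultations, including missed visits. Record attendance at the three physiologist visits as the trial proceeds, so that missed visits are treated alike for both professions and need not be reconstructed later. If a dietitian-only costing is really intended, state that perspective and justify it.

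The change costs one sentence, one further unit cost, and an attendance count for three visits that are already scheduled. Its downside is a somewhat less favourable cost figure for the intervention.

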### Data collection

Standard demographic, clinical and laboratory data (including medication details) will be collected at baseline (1 month) and at 3, 6 and 12 months post-transplant. This will include details of any acute medical issues, clinical or other adverse events, graft function, acute rejection, hospital admissions, development of diabetes, or any other issues that might affect nutritional status or change in weight. Formal study assessments (blinded to group allocation) will be undertaken at baseline (1 month), and at 3, 6 and 12 months (Table 2).

**Table 2 Tab2:** **INTENT study data collection at baseline and months 3**, **6 and 12 post**-**transplant in the intervention and standard care groups**

Type of data	Specific measure
**Demographics**	Age
	Gender
**Clinical status**	Acute medical issues (including acute rejection, hospital admissions, diabetes status)
	Graft function
**Anthropometry**	Body weight
	Body mass index
	Waist circumference & waist-hip ratio
	Mid-arm circumference
	Skin-fold thickness
**Body composition**	Bioimpedance assessment
	Deuterium dilution (total body water, fat mass)
	DEXA (bone mass and fat mass)
	*In vivo* neutron activation analysis of body nitrogen (total body protein)
	Total body potassium (body cell mass)
**Biochemistry**	Serum creatinine
	Estimated GFR
	Immunosuppression drug levels
	Fasting glucose
	Insulin
	HbA1c
	Total, LDL & HDL cholesterol and triglycerides
	Insulin resistance (HOMA)
**Dietary***	3-day food diary
	Motivational assessment rulers to assess motivation to change
**Physical function**	Gait speed assessment
	Hand grip strength
	Sit-to-stand-to-sit test
**Other**	PG-SGA
	NZPAQ-SF
	SF-36
	Blood pressure

*Only collected for intensive arm.

DEXA = Dual-energy x-ray absorptiometry; GFR = Glomerular filtration rate; HbA1c = Haemoglobin A1c; HDL = High density lipoprotein; LDL = Low density lipoprotein; NZPAQ-SF = New Zealand physical activity questionnaire – short form; PG-SGA = Patient-generated subjective global assessment; SF-36 = Short Form-36.

### Anthropometry and body composition

Standardised anthropometric measurements will include body weight, BMI, waist circumference and waist-hip ratio, mid-arm circumference and skin-fold thickness. These will be performed using calibrated instruments stored permanently in the Body Composition Laboratory at the University of Auckland. To ensure standardisation, the same equipment will be used for all measurements in all patients.

Body composition measurements will include gold-standard methods: dual-energy x-ray absorptiometry (DEXA) to determine fat mass [56, 57], total body potassium to assess body cell mass [58], *in vivo* neutron activation analysis for body nitrogen to determine total body protein [59], and deuterium dilution to determine total body water [60]. In addition, bioelectrical impedance assessment will be carried out as a surrogate measurement of total body water, extracellular water and fat mass [61].

### Nutritional status, physical activity and quality of life

Nutritional status will be assessed using the patient-generated subjective global assessment (PG-SGA) [62, 63]. Physical activity will be assessed using the New Zealand Physical Activity Questionnaire – short form (NZPAQ-SF), a modified version of the International Physical Activity Questionnaire (IPAQ) [64, 65]. The Short Form 36 (SF-36) will be used to assess quality of life [66].

### Physical function

The following physical function assessments will be carried out: gait speed, hand grip strength, and sit-to-stand-to-sit test (to assess lower extremity strength) [67–69].

### Biochemistry

During the formal study assessments at baseline (1 month), 3, 6 and 12 months, specific biochemical markers of glucose metabolism and metabolic risk will be measured. Blood samples will be collected after an overnight fast and assayed for glucose, insulin, HbA1c, lipids (including total cholesterol, low density lipoprotein [LDL], high density lipoprotein [HDL] cholesterol and triglycerides) [70]. The homeostatic model assessment (HOMA) index of insulin resistance will be calculated. In addition, where consent is given, serum samples will be stored for the analysis of novel risk factors in the future. Participants and investigators will be blinded to the serum outcomes.

In addition, standard tests will be taken as part of routine post-transplant care, including full blood count, serum creatinine, urea and electrolytes, other biochemistry and samples for therapeutic drug monitoring of tacrolimus or cyclosporine. The results of standard testing will not be blinded.

### Statistical analysis

The primary outcome (body weight at 6 months post-transplant) will be compared between the groups using an analysis of covariance (ANCOVA) adjusted for baseline weight, baseline obesity (BMI ≥ 30 kg/m^2^), and gender. The extent of weight gain after transplant has been shown be significantly affected by baseline BMI [18]; gender will be included as a covariate due to its use as a stratification variable in the randomisation.

Secondary analyses will include analyses of change in anthropometry (BMI, waist circumference, and waist-hip ratio), physical function, body composition, quality of life, and biochemistry parameters between the groups, using ANCOVA with adjustment for relevant baseline covariates. Repeated measures analyses using linear mixed models with multiple covariates will be used to compare changes in weight, anthropometry, physical function, body composition, quality of life, and biochemistry parameters over time (baseline, 3, 6 and 12 months) between the groups. Multiple linear regression will be used to identify significant predictors other than group allocation associated with these changes. Variables identified as significant will be analysed with pairwise comparisons.

Comparisons between groups for differences in variables of interest will be conducted using Fisher’s exact test for categorical variables, unpaired t tests for parametric variables, and Wilcoxon rank sum tests for non-parametric variables.

All statistical analyses will be performed using appropriate statistical software, such as STATA or SAS. The level of statistical significance will be set at probability level of <0.05.

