### Calculation of required sample size

Using Stata statistical software to model an ANCOVA analysis of the primary outcome at six months, with power of 80% and alpha level of 5%, we estimate that 14 participants will be required per group, i.e. 28 in total. To account for dropouts, we aim to recruit up to 32 participants into the study. The effect size was estimated as a weight difference of 5 kg at 6 months between the groups, 74 kg (SD 9 kg) in the standard group and 69 kg (SD 12 kg) in the intervention group. These estimates reflect data from a non-randomised study of intensive nutrition interventions versus standard care in a comparable population of kidney transplant recipients whose weights were similar at baseline [49]. The correlation between weight at baseline and 6 months was estimated as 0.9, based on data showing a mean difference in weight of 3.2 kg (SD 5.9 kg) between 1 and 6 months of 1299 kidney transplant recipients who received their kidney transplant in Auckland between 1991 and 2012 (unpublished observations, data on file), where the correlation was 0.9514. Similar findings were found in an analysis of weight change post-transplant in a comparable population of 156 transplant recipients in Brisbane, Australia (mean weight change 3.3 kg, SD 6.0 kg) ([name], personal communication) [18].

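### Predictors of change are selected on p<0.05 from regressions in about 28 people and then compared pairwise in the same data, so modest effects that are declared significant will be overstated (minor; secondary analysis only)

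*Protocol article*

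**What the plan says.** The relevant text is two consecutive sentences in the Statistical analysis section of the Protocol article. The first reads "Multiple linear regression will be used to identify significant predictors other than group allocation associated with these changes". The second reads "Variables identified as significant will be analysed with pairwise comparisons".

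The changes in question are those of the sentence just before, on mixed models: "changes in weight, anthropometry, physical function, body composition, quality of life, and biochemistry parameters over time (baseline, 3, 6 and 12 months". That is six families of outcomes, most with several measures. The section sets one threshold for everything: "The level of statistical significance will be set at probability level of <0.05".

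The section Calculation of required sample size gives the number of people: "we estimate that 14 participants will be required per group, i.e. 28 in total", and "To account for dropouts, we aim to recruit up to 32 participants into the study". That size was derived for the ANCOVA of six-month weight, not for a search for predictors.

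**The concern.** Under the stated rule, significance decides which variables are called predictors and which go forward to the pairwise step. In a sample this small, that has two consequences.

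- **False predictors.** Each null candidate has a 5% chance of selection, and the search is repeated over many outcomes.
- **Overstated effects.** A variable passes only if its estimated association is large. A true but modest predictor that passes does so because its estimate came out too high.

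The pairwise step cures neither problem, because it uses the same participants in whom the variable was selected. What is at stake is how far the predictors reported for weight, body composition and metabolic change can be believed.

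**Working it through.** **Inputs from the Protocol article.** There are 28 participants (14 per group), with up to 32 recruited. The threshold is p<0.05, taken as two-sided because the article does not say. Group differences at six months are based on 74 kg (SD 9) against 69 kg (SD 12), with a baseline to six-month correlation of 0.9.

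**Assumptions.** The number of candidates, k, is not given, so 5, 10 and 15 are used. The strength b of a true predictor (standardised effect) is not given, so 0.3 and 0.5 are used. Candidates are taken as independent and normal.

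**1. The plan's own sample size.** For ANCOVA, n per arm = (SD₁² + SD₂²)(z₀.₉₇₅ + z₀.₈₀)² / Δ² × (1 − ρ²).

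- (81 + 144) × 2.8016² / 25 = 225 × 7.849 / 25 = 70.64
- 70.64 × (1 − 0.81) = 13.42, rounded up to 14 per arm, or 28 in total

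The stated figure is reproduced, so 28 is the right basis. The allowance up to 32 corresponds to 28/32 = 87.5% retained.

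**2. How large an association must look to be selected.** Critical r = t / √(t² + df).

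| Model at n=28 | df | t | Smallest significant r |
|---|---|---|---|
| One predictor alone | 26 | 2.056 | 0.374 |
| 10 candidates plus group | 28 − 12 = 16 | 2.120 | 0.468 (partial) |

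At n=32 a lone predictor still needs 0.349. A true partial correlation of 0.2 in the 10-candidate model can therefore be significant in its true direction only with an estimate at least 0.468 / 0.2 = 2.3 times its size.

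**3. Chance of at least one false predictor per outcome, all candidates null.** The article specifies multiple regression, so the tests in one model share a residual variance and have few degrees of freedom. The formula for independent tests, 1 − 0.95ᵏ, is then too high. One joint model with group and k candidates was simulated at n=28.

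| k | 1 − 0.95ᵏ | Joint model (simulated) | Expected false predictors, k × 0.05 |
|---|---|---|---|
| 5 | 23% | 21% | 0.25 |
| 10 | 40% | 32% | 0.50 |
| 15 | 54% | 38% | 0.75 |

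The simulated column is the one that fits the stated method.

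**4. One true predictor among k candidates, n=28 (simulated).**

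| k | b | Power to select it | False share of all selected | Inflation when selected |
|---|---|---|---|---|
| 5 | 0.3 | 29% | 41% | 1.8 |
| 10 | 0.3 | 22% | 67% | 2.0 |
| 15 | 0.3 | 17% | 81% | 2.2 |
| 5 | 0.5 | 71% | 22% | 1.2 |
| 10 | 0.5 | 58% | 44% | 1.3 |
| 15 | 0.5 | 44% | 61% | 1.4 |

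**5. The second step.** One possible form of pairwise comparison is a t test across a median split of the selected variable. In that form, a falsely selected predictor was significant again in 19% to 36% of simulated cases at n=28. A test in independent data would give 5%.

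**The case against.** **Some of this is detail that an article leaves out.** The article prints no candidate list and no exploratory label for this analysis. Both may stand in a fuller document, and their absence is not the point. What stands is the rule in print: select on significance, then analyse the selected variables. A fuller plan that followed this text would still do that.

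**Pairwise comparison is undefined.** It may mean ordinary contrasts between levels of a factor or between visits, which describe where a difference lies. A reader might infer that the plan offers this step as confirmation of a predictor. The article does not say so, and the 19% to 36% above applies to one assumed form only. What survives is narrower: on any reading, the step is triggered by significance and reuses the same data.

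**The size depends on unstated inputs.** This is correct. A reader might quote 40% or 54% from the independent-test formula, but the stated method gives about 32% and 38%. A reader might also count some 21 outcome measures from the Statistical analysis section and Table 2 and expect 21 × 10 × 0.05 = 10.5 false predictors. That holds only if all 10 assumed candidates are null for every outcome. With 5 candidates and a strong true predictor, the false share falls to 22% and the inflation to about 1.2 times.

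**Consequence for later research.** A reader might infer that false predictors would shape the larger trial. The documents do not support this. The sections Study aims and hypothesis and Primary and secondary outcomes tie feasibility to the 12-month difference in HbA1c between groups.

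**Importance.** Finding predictors is not among the stated aims or outcomes. This objection stands and limits the severity.

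**Conclusion.** The concern holds as a minor flaw in a secondary analysis. Selection at p<0.05 in about 28 people gives roughly a 21%, 32% or 38% chance of at least one false predictor per outcome, if 5, 10 or 15 candidates are assumed and all are null. Estimates that pass must reach |r| of 0.37 for a lone predictor, or a partial r of 0.47 with 10 candidates plus group, so modest true effects that are declared significant are overstated. The critical values follow from n and the assumed model. The percentages also rest on independent normal candidates.

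The primary ANCOVA is not affected, since its covariates are fixed in advance. Nor are the randomised group comparisons, since the search concerns variables other than group. The finding bears only on how reported predictors may be read.

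**What to change.** Replace the two sentences with a single rule:

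- Fit one regression per outcome that keeps group and a short candidate list named in advance, for example baseline BMI, age and gender. The Statistical analysis section already cites prior support for baseline BMI.
- Report every coefficient with its 95% CI, whatever its p value.
- Label the analysis exploratory.
- Delete the pairwise step that depends on significance.

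This changes analysis wording only, and needs no extra data or participants. The cost is that fewer candidate predictors are explored.
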